### Consent

It is the responsibility of the principal investigator (PI) or delegate at physician level at each site to obtain written informed consent for each participant prior to performing any trial-related procedures. All trial investigators seeking consent must be up-to-date with their GCP training and delegated for the task on the delegation log.

The PIS is provided to facilitate the informed consent process. Two different versions of the PIS will be used (online supplemental material)—one for potential participants of the safety run and the other for potential participants of the RCT part of the trial. This is to make clear to potential participants what their participation will involve and how their results will be used, as this differs between the safety run and RCT. The safety run PIS will only be used during the recruitment period for the safety run. Once recruitment to the safety run is complete and RCT recruitment is initiated, the RCT PIS will be the only version used. Investigators must ensure that they adequately explain the aim, trial treatment, potential risks and benefits of taking part in the trial. The patient should be given sufficient time to read the PIS and to discuss their participation with others outside of the clinical research team. The patient must be given the opportunity to ask questions which should be answered to their satisfaction. The right of the patient to refuse to participate without giving a reason must be respected.

If available, the research team will access Trust interpretation services for an interpreter to translate verbal explanations and/or written patient information. The PIS can be printed in a larger font, and/or read out loud for people who may not be able to adequately understand the written information.

If the patient decides to participate in the trial, they will be asked to initial each consent clause and sign and date the latest ethically approved version of the ICF (online supplemental material). The form must also be signed and dated by the PI or delegate. Details of the informed consent discussions should be recorded in the participant’s medical notes. A copy of the signed ICF and PIS should be provided to the participant, and a copy will be kept in their medical records. The original signed consent forms will be kept in the Investigator Site File. Written informed consent will be obtained prior to conducting any study-related procedures. With the participant’s consent, their GP (general practitioner) will be informed of their enrolment onto the trial.

The routine assessments carried out before transplantation for surgical work-up and the additional research samples being collected at Guy’s Hospital for the trial will form the screening and baseline assessments for the consented participants on the trial. The PI or their delegate will confirm the participant’s eligibility for the trial prior to enrolment/randomisation.

## Randomisation procedure/code break

### Randomisation

Recruiting site personnel will be responsible for randomisation of individual participants in the multi-arm randomised stage.

If safety is met, the remaining participants will be randomised to all doses meeting the safety criteria or placebo on a 1:1:1:1 basis, stratified by centre and donor type (there are two main types of deceased donation—DBD and DCD).

The randomisation service will be provided by King’s College London (KCL) Clinical Trials Unit (CTU).

Once ensuring all inclusion and exclusion criteria (with the exception in some cases of crossmatch results) are met and written informed consent is obtained, the participant must be registered on the MACRO trial database. Following registration of the participant on MACRO, a participant ID will be generated. The participant can then be randomised, using their participant ID, via KCL CTU’s randomisation service made accessible to all the centres via the internet (https://cturandomisation.iop.kcl.ac.uk/index).

A step-by-step guide to registering and randomising a participant will be provided to centres in their site files.

In the event of a drug kit number being assigned, and the transplant not going ahead, the pack must be quarantined in the area pre-designated for quarantined kits, until it can be reassigned for use. The coordinating centre should be informed as a matter of urgency if this situation arises so the unused drug kit can be reassigned for future use.

### Emergency code break

While the safety of participants in the trial must always take priority, maintenance of blinding is crucial to the integrity of the trial. Investigators should only break the blind when information about the participant’s trial treatment is clearly necessary for the appropriate medical management of the participant.

Should an alternative to unblinding not be identified, and if unblinding is required to optimise medical management of the participant, investigators should follow the emergency unblinding process below.

24 hours Emergency Code Break and Medical Information will be provided by the Emergency Scientific Medical Service. The investigator and treating physician will have the primary right to break the blind at any moment in case of emergency, and they will be able to unblind immediately and without delay. Each randomised participant will be provided with a card detailing code break telephone numbers and emergency contact details. Participants will be requested to carry this card with them at all times while participating in the trial.

## Withdrawal of participants

Participants have the right to withdraw from the study at any time for any reason. The investigator also has the right to withdraw participants from the study in the event of intercurrent illness, AEs, serious adverse events (SAEs), protocol violations, administrative or other reasons. It is understood by all concerned that an excessive rate of withdrawals can render the study un-interpretable; therefore, unnecessary withdrawal of participants should be avoided. Should a participant decide to withdraw from the study, all efforts will be made to report the reason for withdrawal as thoroughly as possible. A withdrawal visit should be arranged if agreed with the participant.

Withdrawn participants will be replaced with provision for a 10% drop-out rate.

In the event that the participant withdraws from the trial, the appropriate withdrawal page in the eCRF should be completed. On the withdrawal page the Investigator should record the date of the withdrawal and the reason for withdrawal. Data already collected prior to the withdrawal will be retained and this will be made clear in the PIS and ICF.

Death of a participant during the trial will be assessed by the independent DMC as soon as possible to determine whether the trial should be halted. If the cause of death of a participant is deemed unrelated to the trial, they may be replaced in the analysis by another eligible patient.

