## Preparation of the kidney and administration of Mirococept

The following will take place in the operating theatre and will be undertaken by delegated study personnel:

Using 1000 mL of the cold storage solution, the first 500 mL will be used to flush the organ prior to administration of the IMP (investigational medicinal product). Currently, two cold storage solutions are available on the market: University of Wisconsin and histidine-tryptophan-ketoglutarate solution. We have tested the stability of Mirococept in both solutions, and it was found to be equally stable in both (data from these stability studies provided in the Investigator’s Brochure (IB). During the trial, only one cold storage solution will be used across all sites for every participant recruited to the study.The kidney will be placed in a container of ice slush for bench work.The vials of IMP take approximately 15 min to thaw, so should be removed from the dedicated −20°C freezer and thawed by standing at room temperature and then manually swirled initially, again after a further 10 min and finally checked visually. After this time, the solutions should be clear or slightly opalescent.While the kidney is in ice slush, all six vials of the IMP kit should be drawn up from the participant’s allocated drug kit and added into the remaining 500 mL of the cold storage solution (500 mL should be left in the 1000 mL bag following the initial 500 mL flush).Used vials should be discarded in the theatre sharps bin and destroyed as per local standard operating procedures (SOPs). The empty kit box should be retained for accountability checking by the clinical research associate.Vial box tear-off label should be removed and affixed to the printed randomisation email for reconciliation purposes.The Mirococept or placebo perfusion bag should be affixed with the appropriate label.Once the IMP/placebo is mixed with the cold storage solution, the fluid is then perfused through the kidney via the renal artery(s), under 1 m hydrostatic pressure.The perfusion will be conducted via a cannula held in place manually such that as much perfusion solution as possible drains through the kidney.If there is more than one renal artery, and they are of sufficient size, the IMP should be distributed equally through each of the arteries according to their estimated proportion of the kidney that they vascularise.The administration of IMP should take approximately 15 min.Following perfusion, the cannula is removed and the kidney repacked for cold storage.No post perfusion flush or arterial or renal vein clamping will be required.The transplantation procedure will continue in the standard manner.

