### Assessment of safety

Specification, timing and recording of safety parameters

The following safety parameters will be collected at every visit.

AEs and concomitant treatment profile.Vital signs to include:Blood pressure, heart rate, respiratory rate, temperature, oxygen saturation, weight (required at day 0, desirable for subsequent visits) and height (only required at day 0).Haematology to include:Haemoglobin, platelets, haematocrit, red blood cells, mean cell volume, white blood cell, lymphocyte, basophil, monocyte, neutrophil, eosinophils.Serum biochemistry to include:Glucose, gamma-glutamyl transferase, potassium, sodium, creatinine, eGFR, total bilirubin, bicarbonate, alkaline phosphatase, phosphorus, total protein, magnesium, AST (aspartate aminotransferase)/ALT (alanine aminotransferase), albumin, calciumUrinalysis to include:Protein, specific gravity, glucose, pH, ketones, leucocytes, nitrites, urine sediment.Urine microscopy and culture.Tacrolimus blood levels.

The Investigator will review all laboratory reports and will sign and date them on the day of review. If there are any findings outside the normal range, the investigator will confirm whether the result is clinically significant or not. Any laboratory report indicated as being clinically significant will be recorded on the AE section of the eCRF.

AEs will be recorded from consent up until the end of a participant’s 12-month follow-up period. All SAEs will be followed-up for a further 30 days after the last participant’s final 1-year follow-up visit date or until resolution.

All SAEs, serious adverse reactions and suspected unexpected serious adverse reactions (SUSARs) will be reported immediately (and certainly no later than 24 hours) by the Investigator to the King’s Health Partners-Clinical Trials Office (KHP-CTO) and chief investigator (CI) for review in accordance with the current pharmacovigilance policy. The KHP-CTO will report SUSARs to the relevant ethics committee and to the Medicines and Healthcare products Regulatory Agency (MHRA).

Reporting timelines are as follows:

SUSARs which are fatal or life-threatening must be reported not later than 7 days after the sponsor is first aware of the reaction. Any additional relevant information must be reported within a further 8 days.SUSARs that are not fatal or life-threatening must be reported within 15 days of the sponsor first becoming aware of the reaction.

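### After the kidney has been perfused, AEs and SAEs remain grounds for the investigator to withdraw a participant from the study, which risks losing later safety and 12-month outcomes in those who had a harm

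*Protocol article*

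**What the plan says.** All references are to the protocol article.

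- **Withdrawal of participants** gives the investigator a right that applies to the study, not to treatment: "The investigator also has the right to withdraw participants from the study in the event of intercurrent illness, AEs, serious adverse events (SAEs". The list continues with protocol violations and with administrative and other reasons. The section cautions that "unnecessary withdrawal of participants should be avoided", because too many withdrawals could make the study impossible to interpret.
- The same section then provides for these steps: "A withdrawal visit should be arranged if agreed with the participant"; a date and reason on the eCRF withdrawal page; and "Data already collected prior to the withdrawal will be retained and this will be made clear in the PIS and ICF". Withdrawn participants are to be replaced, within a 10% drop-out provision.
- **Preparation of the kidney and administration of Mirococept** describes one perfusion of the donor kidney before implantation: "The administration of IMP should take approximately 15 min". No later dosing is described.
- **Assessment of safety** sets the recording window: "AEs will be recorded from consent up until the end of a participant", where the sentence ends at the 12-month follow-up. It adds: "All SAEs will be followed-up for a further 30 days", counted from the last participant's final 1-year visit, or until resolution. Neither sentence mentions withdrawn participants.
- **Trial assessments** says the scheduled assessments are routine transplant care, except for research samples taken at Guy's Hospital.

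**The concern.** Withdrawal for an adverse event suits a drug given repeatedly, where it may go with stopping further doses. Here exposure is complete before the organ is implanted. From then on, withdrawing someone because of an AE or SAE cannot reduce exposure to the trial product, and it spares little burden because the follow-up is largely routine. Its main practical consequence is that the participant may no longer contribute data, for a reason tied to the outcomes under study.

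The primary objective is to find the most safe and efficacious dose. Both the section on the multi-arm randomised trial and the Analysis section bring safety outcomes into the choice between doses, with secondary outcomes added where doses look alike. If follow-up ends more often in participants with complications, a dose that produces more complications could show fewer later ones than it caused. Recruiting a replacement restores the number of participants but not the missing information.

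**Working it through.** The point is mainly textual, so the sections are set side by side first. The arithmetic only gives a scale.

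**1. What survives a withdrawal for an SAE after perfusion**

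- *The triggering event.* It was recorded before withdrawal, so it is retained. Under Assessment of safety all SAEs are followed, with no exception for withdrawn participants. This event is not lost.
- *Later AEs and new SAEs.* Assessment of safety implies recording to 12 months. Withdrawal of participants names only data already collected. Neither section says which governs.
- *Later endpoints* (Secondary endpoints): primary non-function over 3 months, biopsy-proven rejection at 6 and 12 months, GFR at 12 months, and 1-year graft and patient survival. Nothing in the withdrawal section provides for collecting these afterwards.
- *Primary endpoint.* It is complete at day 7, so only a withdrawal before then can affect it.

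**2. The plan's own allowance for drop-out (Sample size)**

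Inputs: 36 per arm, 4 arms, 10% drop-out.

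N = 144 / (1 − 0.10) = 160, or 40 per arm. The stated figure is reproduced. The allowance is 40 − 36 = 4 participants per arm, for drop-out of any kind. It is not an estimate of harm-related withdrawal.

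**3. Scale for a 12-month yes/no outcome**

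- On the analysed target, one participant is 1/36 = 2.8 percentage points of an arm's rate.
- On the randomised target, if L of 40 have no outcome and x events are seen in the rest, the arm's true proportion lies between x/40 and (x + L)/40, a width of L/40. For L = 1, 2 and 4 this gives 2.5, 5 and 10 points.

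The value of L that investigator withdrawals would produce is unknown.

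**4. Scale for the primary endpoint (illustration, assumed counts)**

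Suppose 12 of 40 have DGF (30%), and 4 are withdrawn before day 7 and left out. If a of those 4 had DGF, the observed rate is (12 − a)/36:

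- a = 0: 12/36 = 33.3%
- a = 4: 8/36 = 22.2%

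This requires very early withdrawal and no record of dialysis status.

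**5. Safety run**

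There are three participants per dose, drop-outs are replaced, and one trigger for formal review by the Data Monitoring Committee (DMC) is two or more in a group with DGF beyond 2 weeks. If two would have met this and one were withdrawn before 2 weeks without further follow-up, the count would be 2 − 1 = 1 and the trigger would not be met.

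**The case against.** The case on the other side is substantial, and several parts of it stand.

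- *The article never says that collection stops.* A reader might infer that only data from before withdrawal are kept. The text says "Data already collected prior to the withdrawal will be retained", without the word only, and the sentence stands in a paragraph about a participant who withdraws. The article is silent on what follows an investigator's withdrawal, and the full protocol may fill that silence. This stands, so the point rests on the stated right to withdraw for harm, not on the silence.
- *The two sections do not flatly contradict each other.* A reader might infer that SAE follow-up ends with withdrawal. The documents do not support that, because follow-up of all SAEs can be read as covering withdrawn participants. What remains is that the sections do not settle AE recording to 12 months or new events.
- *The grounds have a proper use.* Consent and randomisation may precede the cross-match result, and a transplant may not go ahead after a kit is assigned (Table 2; Randomisation). Intercurrent illness or an eligibility problem before perfusion is an ordinary reason to withdraw someone. After transplantation, withdrawal can also end research-only sampling. This stands and rules out simply deleting the grounds.
- *There are safeguards.* The right is permissive, unnecessary withdrawal is discouraged, deaths go to the DMC, and the DMC reviews safety data after each safety-run cohort and can meet at any time its chair sees fit. These reduce the risk. However, the discouragement concerns the rate of withdrawals and does not say that withdrawal for an AE or SAE is unnecessary.

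That the analysis plan could deal with this does not stand. An analysis can model missing outcomes, but it cannot recover events that were never collected.

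**Conclusion.** The point holds in a limited form. After perfusion, the stated grounds permit withdrawal from the study for a harm when no trial treatment is left to stop. The information at risk is later AEs and SAEs and the 3- to 12-month outcomes, and in the safety run possibly the 2-week DGF count. The triggering SAE is not at risk.

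The size of any bias cannot be derived from the documents. Each lost participant is 2.8 points at 36 per arm. The bounds above show what a given number of losses could hide, not what will happen. A reader might go further and infer that a harmful dose would appear to have a stated fraction of its true event rate; no figure in the article supports such a fraction.

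The conclusion assumes that investigators use the right after perfusion and that withdrawal is then treated as the end of data collection, which the article neither states nor excludes. The change is worth making because it is cheap and the loss would be irreversible. It alters no sample-size figure.

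**What to change.** In Withdrawal of participants:

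1. Keep the listed grounds for the period from consent until perfusion of the kidney with trial product.
2. State that after perfusion AEs, SAEs, intercurrent illness and protocol violations are not grounds for ending data collection, and that only the participant's own withdrawal of consent ends it.
3. State that dialysis status, AEs and SAEs, graft status and vital status continue to be collected to 12 months from routine care, together with rejection and 12-month GFR where routine care records them. Research-only sampling may stop.
4. Reconcile this section with Assessment of safety by saying in both whether AE recording to 12 months and SAE follow-up apply after withdrawal.

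The cost is a protocol amendment, a change to the eCRF withdrawal page so that it separates withdrawal of consent from other reasons, a check that the information sheet and consent form agree, and some extra data entry. No additional visits should be needed, because the follow-up data come from routine transplant care.

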### Secondary endpoints

Functional DGF—failure of serum creatinine to decrease by at least 10% daily on three consecutive days in week 1 post-transplantation (excludes patients with biopsy-proven rejection or calcineurin inhibitor (CNI) toxicity in week 1 post-transplantation).Number of dialysis sessions during the first 30 days post-transplantation.Duration of DGF.Mean calculated GFR (glomerular filtration rate) (Chronic Kidney Disease Epidemiology Collaboration) at 12 months post-transplantation.Mean calculated creatinine clearance (Cockcroft-Gault) at 12 months post-transplantation.Primary non-function—permanent lack of graft function for 3 months post-transplantation.AUC of serum creatinine on days 1–14 post-transplantation.Biopsy-proven acute rejection at 6 and 12 months post-transplantation.Biopsy-proven CNI toxicity within 12 months post-transplantation.Duration of post-transplantation hospital stay.Number and duration of any hospital admissions during the first 12 months post-transplantation.1-year graft survival (censored and uncensored for death with functioning allograft).1-year patient survival.

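### A death judged unrelated may be replaced in the analysis: a discretionary post-randomisation exclusion that biases the one-year survival endpoints upward

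*Protocol article*

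**What the plan says.** All references are to the protocol article; the statistical analysis plan is not shown.

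- **Deaths (Withdrawal of participants).** The scope is general: "Death of a participant during the trial will be assessed by the independent DMC as soon as possible", to decide whether the trial should be halted. If the cause is "deemed unrelated to the trial, they may be replaced in the analysis by another eligible patient". The text does not say who makes that judgement or by what criterion.
- **Withdrawals (same section).** "Withdrawn participants will be replaced with provision for a 10% drop-out rate". On data, "Data already collected prior to the withdrawal will be retained". The article speaks of replacement in the analysis only for deaths.
- **Endpoints (Secondary endpoints).** The list includes "1-year patient survival" and "1-year graft survival (censored and uncensored for death with functioning allograft").
- **Timing (Multi-arm randomised placebo-controlled trial).** DGF is assessed at seven completed days after transplantation, and follow-up lasts 12 months.
- **Sample size.** 36 per arm (144) is inflated for 10% drop-out to 40 per arm (160).

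**The concern.** A randomised comparison is protected only while the analysed arms are the arms that were randomised. Here a participant who was allocated, received a treated kidney and was observed can be taken out because of a later event, on a judgement about its cause, with the word *may* leaving each case open. The incoming patient is not a substitute in any statistical sense. Allocation is blinded, stratified and 1:1:1:1, so the next patient randomised need not fall in the same arm.

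Two results are exposed. Patient survival, and graft survival uncensored for death, count deaths whatever their cause, and the rule removes some of them. The primary outcome is fixed at day 7, so replacing a later death throws away a known DGF result. The Background section links DGF to a higher risk of death, so the discarded results need not be a random sample.

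This is a stated rule, not detail left to the analysis plan. An analysis plan could only repeat it or contradict it.

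**Working it through.** **1. The plan's own figures.** Inflation: 144/(1 − 0.10) = 160 and 36/0.90 = 40, as stated. The exact binomial probability of correct selection (rates 0.30 and 0.50, ties broken at random) is 0.9032 with four arms of 36 and 0.8985 with 35. So 36 is the smallest size reaching 90%. The fallback sizes also reproduce: 0.9034 for three arms of 30 and 0.9027 for two arms of 20. Recruiting 160 and losing 10% leaves 144, so replacement in the analysis is not needed to keep the 90%.

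**2. Does the rule reach the randomised stage?** It covers any death during the trial. The safety run has its own replacement rule for drop-outs (Safety run), and its participants are kept out of the RCT analysis. Nothing limits the death sentence to that stage.

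**3. Survival endpoint.** Let *m* be true one-year mortality and *u* the share of deaths judged unrelated and replaced. The article gives neither, so both are assumed. If each such death is replaced by a new participant under the same rule, the analysed set is conditional on not being an unrelated death, which has probability 1 − *mu*. The deaths still counted have probability *m*(1 − *u*). Hence

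reported survival = 1 − *m*(1 − *u*)/(1 − *mu*).

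For *m* = 5% and *u* = 50%: 1 − 0.025/0.975 = 97.4%. For *u* = 80%: 1 − 0.01/0.96 = 99.0%.

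| True mortality (assumed) | True survival | *u* = 50% | *u* = 80% | *u* = 100% |
|---|---|---|---|---|
| 2% | 98.0% | 99.0% | 99.6% | 100% |
| 5% | 95.0% | 97.4% | 99.0% | 100% |
| 10% | 90.0% | 94.7% | 97.8% | 100% |

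**4. Primary endpoint.** Replace one DGF case in an arm of 36 by a new participant whose expected rate is the arm's own rate *p*. The arm's rate falls by (1 − *p*)/36:

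- *p* = 0.50: 0.50/36 = 1.4 points; two cases, 2.8 points.
- *p* = 0.30: 0.70/36 = 1.9 points; two cases, 3.9 points.

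At 5% mortality an arm of 36 expects 36 × 0.05 = 1.8 deaths. One or two deaths, all in DGF cases and all replaced, give a shift of 1.4 to 3.9 points against a planned difference of 20.

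Replacing a death without DGF moves the rate the other way, by *p*/36 (1.4 points at 50%, 0.8 at 30%). For the average, suppose the relative risk of death of 1.64, given for five years in Background, also held at one year (an assumption). In a 50% arm, 1.64/2.64 = 62% of deaths would then be DGF cases. The mean shift per replaced death would be (0.62 − 0.50)/36, about 0.3 points downward. The average bias in DGF is therefore small, and the 1.4 to 3.9 points describe an unfavourable case.

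**The case against.** The best defence is that the sentence is permissive, covers only deaths judged unrelated, and would touch perhaps one or two participants per arm in a Phase IIa selection trial with a day-7 primary endpoint. Recruitment to the RCT is planned for about 12 months and follow-up runs on until the last recruit reaches 12 months, so many late deaths could not in practice be replaced. Adverse events are recorded from consent to 12 months, and every death triggers review by the data monitoring committee. Replacement also has a proper use, since a participant may be randomised and the transplant then not go ahead.

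Most of this stands as a limit on size. It does not rescue the rule. A rule applied only to deaths that occur while recruitment is open adds a further arbitrary selection. Allowing for transplants that do not proceed needs no provision about deaths.

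Stronger readings are tempting, and the documents do not support them:

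- **Withdrawals.** A reader might infer that withdrawn participants are also swapped in the analysis, especially as investigators may "withdraw participants from the study in the event of intercurrent illness, AEs, serious adverse events (SAEs), protocol violations, administrative or other reasons" and the abstract describes 36 per arm as net of drop-outs. Taking the 10% provision as 4 of 40, one could then compute DGF shifts of 5 points (4 × 0.50/40) to 10 points (4/40). But the withdrawal sentence does not mention the analysis, earlier data are kept, and the 10% matches the inflation from 144 to 160. Extra recruitment is the natural reading, so those shifts do not follow from the stated rule.
- **Emptied endpoints.** A reader might infer that the survival endpoints lose all their events. That happens only if every death is judged unrelated and replaced.
- **Safety data.** A reader might infer that deaths vanish from the safety comparison. Nothing removes them from adverse-event recording or committee review.

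**Conclusion.** The point holds for the death sentence. As written, it permits exclusion of randomised participants on a post-treatment causality judgement, with no limit to the safety run. The certain consequence is directional: wherever the rule is used, patient survival and death-uncensored graft survival are reported too high. At an assumed 5% mortality the overstatement is 2.4 points if half the deaths are replaced (97.4% against 95.0%) and 5 points if all are. For DGF, one or two replaced cases in an arm of 36 move its rate by about 1.4 to 3.9 points. The size and direction depend on who dies, and the expected shift is smaller. Mortality, the share judged unrelated and the DGF status of those who die are all assumptions.

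How a week-1 death counts in the primary endpoint, and how freely investigators may withdraw participants, are separate questions that this sentence does not settle.

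**What to change.** - For the randomised stage, delete the sentence on replacement in the analysis, or state that replacement means additional recruitment only.
- State that every randomised and transplanted participant is analysed in the allocated arm, and that all deaths, whatever the attributed cause, count in one-year patient survival and death-uncensored graft survival.
- Add one line confirming that the 10% drop-out provision is recruitment inflation (144 to 160), and that the retained data of withdrawn participants, including any day-7 DGF result, stay in the analysis.

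The cost is a short protocol amendment with matching wording in the analysis plan, made before any RCT analysis. No extra patients are needed: 160 recruited less 10% is already 144.
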